### Interim analysis

When an adequate number of patients are enrolled and followed-up, interim analysis will be performed. When data are included for the full analysis set and recorded in the database, the first interim analysis during the management period will be performed to check whether the core data collected are suitable for preliminary significant data analysis. According to research progression, subsequent interim analysis of all data included in the database will then be designated. After acquiring approval from the Department of General Surgery and Scientific Construction Committee, the Fourth Affiliated Hospital of China Medical University, the data collected in the Department of General Surgery, the Fourth Affiliated Hospital of China Medical University are likely to be analysed together with the data collected from the other research centres. In accordance with applicable laws and regulations, the information on the subjects in the study will be kept confidential. The data for interim analysis will be precisely described in a statistical analysis plan. The interim analysis results will be submitted to an independent data monitoring committee in the form of a statistical analysis report and as slides.

### Sample size

According to previous reports,^22 23^ we hypothesised that the incidence of chronic inguinal pain after anterior transversalis fascia repair and preperitoneal space approach was 10% and 3.4%, respectively. Taking α=0.05 and power=90%, the final effective sample size of n=600 was calculated. Assuming a patient loss rate of 20%, we require 720 patients.

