**Methods and analysis:**

This will be a prospective, large sample, multicentre, randomised, controlled trial. Registration date is 1 December 2016. Actual study start date is 6 February 2017. Estimated study completion date is June 2020. A cohort of over 720 patients with inguinal hernias will be recruited from nine institutions in Liaoning Province, China. Patient randomisation will be stratified by centre to undergo inguinal hernia repair via the anterior transversalis fascia approach or the preperitoneal approach. Primary and secondary outcome assessments will be performed at baseline (prior to surgery), predischarge and at postoperative 1 week, 1 month, 3 months, 1 year and 2 years. The primary outcome is the incidence of postoperative chronic inguinal pain. The secondary outcome is postoperative complications (including rates of wound infection, haematoma, seroma and hernia recurrence).

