### Randomisation and blinding

This study is a multicentre trial, so stratified block randomisation will be performed in each centre. A randomisation sequence table will be generated by a statician who will not be involved in the trial using Statistical Analysis System (SAS V.9.1). The serial numbers assigned to each patient will be preserved in opaque sealed envelopes. The sealed envelopes will be subsequently given to the trial centre. All patients will not know the surgical regimen until after the surgery. The surgeons will not be blinded to the surgical regimen. Outcome assessors will be blinded to the surgical records in the electronic case report form (eCRF).

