## Discussion

### Significance of this study

This study will be the first large sample (720 patients), multicentre, randomised, controlled, clinical trial to investigate the effectiveness of inguinal hernia repair via the anterior transversalis fascia approach versus the preperitoneal approach in patients from northern China. In this study, postoperative complications will be used as the primary outcome measure, and patient quality of life and cost-utility analysis will be the secondary outcome measures.

However, this study is also limited: (1) Although all surgeons involved in the study will receive training of standard surgical procedure, confounding variables including surgeon’s clinical experiences and surgical conditions should be considered to reduce the bias in the estimate of the study outcomes. (2) The time taken for studying postoperative recurrence of inguinal hernia is limited, which likely influences the judgement of long-term recurrence of inguinal hernia.

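### The 20% loss allowance multiplies 600 by 1.2 instead of dividing by 0.8, so 720 patients leave 576 evaluable, not the 600 required

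*Protocol article*

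**What the plan says.** The protocol article, Sample size, assumes that "the incidence of chronic inguinal pain after anterior transversalis fascia repair and preperitoneal space approach was 10% and 3.4%, respectively". With α of 0.05 and 90% power it reports that "the final effective sample size of n=600 was calculated", and it closes with "Assuming a patient loss rate of 20%, we require 720 patients".

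The recruitment figure recurs elsewhere without further derivation. The abstract (Methods and analysis) says "A cohort of over 720 patients with inguinal hernias will be recruited from nine institutions", and Study design uses the same form of words. The Discussion (Significance of this study) gives the plain figure: "This study will be the first large sample (720 patients". No other loss rate and no larger target appears anywhere in the article.

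**The concern.** The plan calls 600 the effective size and then adds an allowance for loss, so 600 is the number that must still be evaluable after loss. A loss rate is a share of the patients recruited. The step from 600 to 720 instead adds 20% of the number to be retained, which is a smaller allowance than a 20% loss requires.

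If so, a trial that runs exactly as assumed ends below its own evaluable target. Someone overseeing follow-up would also accept 20% loss as within plan, although the 600 is already missed once loss passes a lower figure. The loss matters for the primary outcome in particular, because chronic pain is assessed at 1 and 2 years by telephone (Primary outcome measure; Follow-up), so a patient lost before then contributes no primary data.

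**Working it through.** **Inputs from the protocol article, Sample size:** p1 = 0.10 (anterior transversalis fascia), p2 = 0.034 (preperitoneal), α = 0.05, power 90%, effective size 600, loss 20%, recruited 720.

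**Assumptions, because the article does not state them:** two-sided test and 1:1 allocation. They matter only for reproducing the 600 and for the power figures. The loss arithmetic uses neither.

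**1. Reproduce the 600.** Normal approximation, pooled variance under the null, no continuity correction:

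n per arm = [z(0.975)·√(2·p̄·(1−p̄)) + z(0.90)·√(p1(1−p1) + p2(1−p2))]² / (p1−p2)²

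- p̄ = (0.10 + 0.034)/2 = 0.067 and p1−p2 = 0.066
- n = [1.96·√(2 × 0.067 × 0.933) + 1.2816·√(0.10 × 0.90 + 0.034 × 0.966)]² / 0.066² = 299.5
- Rounded up: 300 per arm, **600 in total**. This matches the plan.

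Other common choices fit less well: unpooled variance gives 594, arcsine 566, continuity-corrected 660, and one-sided (pooled) 488.

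**2. Trace the 720.**

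- 600 × (1 + 0.20) = **720**, the plan's figure.
- 600 / (1 − 0.20) = **750**, the number that leaves 600 after 20% loss (750 × 0.80 = 600).

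**3. What 720 delivers.**

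- Evaluable at 20% loss: 720 × 0.80 = **576**, or 288 per arm.
- Shortfall: 600 − 576 = **24** (24/600 = 4%).
- Largest loss that still leaves 600: 1 − 600/720 = **16.7%** (120 of 720 patients; 20% would be 144).

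**4. Power at 576.** Solving the formula in step 1 for power, with 288 per arm:

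z = [0.066·√288 − 1.96·√(2 × 0.067 × 0.933)] / √(0.10 × 0.90 + 0.034 × 0.966) ≈ 1.22, so power = **88.8%** (0.8885 before rounding). At 300 per arm the same formula gives 90.0%.

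**5. Exact power for the tests the plan names.** Statistical analysis allows χ² or Fisher's exact test for the primary outcome. Exact unconditional power at the planned rates:

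| Test | 300 per arm | 288 per arm |
|---|---|---|
| Pearson χ², uncorrected | 91.7% | 90.6% |
| Fisher's exact | 88.4% | 86.9% |

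The shortfall costs 1.1 to 1.5 percentage points with either test.

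**The case against.** The arithmetic is hard to contest; the case on the other side is about how much it matters.

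- **The effect is small.** It amounts to 24 patients and about 1.2 points of power by the planning formula. No estimate or conclusion is likely to turn on that. This stands.
- **90% power can survive.** For the uncorrected χ² test, named first in Statistical analysis, exact power at 288 per arm is 90.6%. With about 19 expected events per arm (0.067 × 288 = 19.3), the usual small-count reason for Fisher's test would not arise. Fisher's test is below 90% even at the full 600, so most of its deficit comes from the choice of test. This also stands, and it limits the claim: the three figures that cannot be reconciled are 600 evaluable, 20% loss and 720 recruited. It does not repair them, because the plan defined its requirement as 600.
- **Some wording permits more than 720.** The abstract and Study design leave room for a higher number, so recruiting 750 is not barred. But they set no higher target, and Sample size and the Discussion both give 720.
- **Loss may stay below 20%, and analysis is by intention to treat.** At 16.7% or less there is no shortfall. But 20% is the plan's own assumption. Naming intention to treat does not supply outcomes for patients who were lost, and the section on completion and withdrawal excepts those lost to follow-up from evaluation of the last visit. How missing outcomes are handled may be set out in an analysis plan that is not shown; that would not change the stated sum.
- **A 20% mark-up is a common shortcut.** The text speaks of a loss rate among patients, not of a 20% increase in recruitment, so this reading does not fit.

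**Conclusion.** The concern holds. The base figure of 600 is sound, but the inflation to 720 is wrong for the stated loss rate. At 20% loss the plan leaves 576 evaluable patients, 24 (4%) fewer than it says it needs. The loss it can absorb is 16.7%, and keeping 600 would take 750. By the formula that gives 600, power is 88.8% rather than 90.0%.

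The error in the 600, 20% and 720 figures is certain and rests on no assumption beyond reading the loss rate as a share of those recruited. The power figures also rest on a two-sided test, equal allocation, loss spread evenly over the arms and the planned rates being true. The consequence is a modest overstatement in a headline design figure. It calls for correcting the statement, not for redesigning the trial.

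**What to change.** Correct the last sentence of Sample size. Either remedy is adequate.

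- **Restate what 720 provides.** For example: 720 randomised patients leave 600 evaluable if loss is at most 16.7%; at 20% loss, 576 are evaluable and power is about 89% by the planning formula. Follow-up losses should then be judged against 16.7%, not 20%. Cost: one sentence and a slightly less favourable power statement, with no extra patients.
- **Keep both 20% loss and 90% power.** State a target of 750 and align the abstract, Study design and Discussion with it. Cost: 30 more patients. The article reports that recruitment was still open at submission, and its wording elsewhere already permits more than 720.

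Whichever is chosen, stating the sidedness of the test and the allocation ratio beside the calculation would let a reader reproduce the 600 without guessing.

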### Ethics and dissemination

#### Ethical approval

Before study commencement, the following files will be provided to the Independent Ethics Committee (IEC):Final draft of study protocol (and supplements);Sponsor-approved informed consent and other documents provided to the subjects (such as participation card and diary card);Materials assisting patients to be included;Materials regarding study-related injury compensations or rewards for patient participation in the study;Researcher résumé or equivalent (unless the IEC states that this is not needed);Sponsor name, funds, potential competing interests and information that affects patient participation in the study;Any other documents required by the IEC.

Trials cannot be started until the IEC completely approves the study protocol, informed consent, materials assisting patients to be included and compensation measures for the patients, and the sponsor receives a copy of the IEC approval document(see online supplementary file 3). The IEC approval document should include the trial title (registration number), name of the study file (including edition code) and date of approval.

10.1136/bmjopen-2017-016481.supp3Supplementary file 3

During the study period, it is likely that researchers will submit the following files to the IEC for approval at appropriate time-points:Supplement of study protocol;Informed consent forms and documents regarding rewards for patient participation in the study;New information that is likely to negatively affect participant safety and study progression;Files regarding bias and alterations of the study protocol made to avoid immediate injury to patients;Reports regarding dead patients;Notification of change of project manager;Other requirements of the IEC.

If the supplemented study protocol increases the risk to patients, the supplemented study protocol and corresponding modified informed consent form will be submitted to the IEC for consideration. The supplemented study protocol will not be performed until approval from the IEC is obtained. The major study protocol was approved by the IEC, the Fourth Affiliated Hospital of China Medical University (approval number 2015–027) on 27 November 2015. The study protocol should be reviewed by the IEC at least once every year, and the reviewed suggestion will be recorded on paper. At the end of the study, the researchers should inform the IEC of its completion.

We began recruitment in February 2017 and expect to have completed recruitment by December 2019 and completed data collection by June 2020. The final results of the trial will be published in international peer-reviewed journals.

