### Follow-up

Visit 3 (1 week after surgery via clinic visit or telephone follow-up)36-Item Short Form Health Survey (SF-36) score;Medical costs;Hernia recurrence (date and severity of recurrence). Recurrence will be diagnosed by the medical institutions, after being alerted by patients that symptoms are present.Presence or absence of haematoma and/or seroma;Wound infection (date and severity of wound infection).

Visit 4 (1 month after surgery via clinic visit or telephone follow-up)SF-36 score;Medical costs;Hernia recurrence (date and severity of recurrence). Recurrence will be diagnosed by the medical institutions, after being alerted by patients that symptoms are present.Presence or absence of haematoma and/or seroma;Wound infection (date and severity of wound infection).

Visit 5 (3 months after surgery via clinic visit or telephone follow-up)SF-36 score;Medical costs;Hernia recurrence (date and severity of recurrence). Recurrence will be diagnosed by the medical institutions, after being alerted by patients that symptoms are present.Presence or absence of haematoma and/or seroma;Wound infection (date and severity of wound infection).

Visit 6 (1 year after surgery via telephone follow-up)VAS pain score;SF-36 score;Medical costs;Hernia recurrence (date and severity of recurrence). Recurrence will be diagnosed by the medical institutions, after being alerted by patients that symptoms are present;Presence or absence of haematoma and/or seroma;Wound infection (date and severity of wound infection).

Visit 7 (2 years after surgery via telephone follow-up)VAS pain score;SF-36 score;Medical costs;Hernia recurrence (date and severity of recurrence). Recurrence will be diagnosed by the medical institutions, after being alerted by patients that symptoms are present;Presence or absence of haematoma and/or seroma;Wound infection (date and severity of wound infection).

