### Outcome measures

#### Primary outcome measure

To reduce the outcome bias of a single evaluation, the incidence of chronic pain at 1 and 2 years after surgery will be evaluated. According to International Association for the Study of Pain, VAS pain score >0 for over 3 successive months indicates chronic inguinal pain.^20^

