#### Other outcome measures.

Quality of life is evaluated by the SF-36.^21^The SF-36 is a 36-item, patient-reported survey of patient health. It consists of eight scaled scores, including vitality, physical functioning, bodily pain, general health perceptions, physical functioning, emotional functioning, social functioning and mental health. The score of each scale is summed and then standardised according to the formula: standardised score = (actual raw score—lowest possible raw score)/possible raw score range×100. The total SF-36 score is the standardised score based on the sum of the eight scaled scores. A higher score indicates better quality of life.

The cost utility analysis of therapeutic regimens involving different surgical approaches will be analysed. Medical costs consist of direct medical and non-medical costs. The direct medical costs include drug charges, inspection fees, laboratory fees, treatment fees, nursing fees and bed charges. The direct medical costs during hospitalisation will be calculated according to the hospital information system. Direct medical costs during the follow-up period will be reported by patients and/or their relatives. Direct non-medical costs include payments for transportation to receive medical care, cost of nutritional supplementation and the costs for accompanying family members during the treatment period.

All outcome evaluations will be independently performed by an experienced assessor blinded to the treatment regimens. The schedule of outcome measurement assessment is shown in table 3.

**Table 3 T3:** Timing of outcome measurement assessment

	Before surgery	During surgery	Follow-up				
	Visit 1 (at admission, day 0)	Visit 2 (at discharge)	Visit 3 (1 week after surgery)	Visit 4 (1 month after surgery)	Visit 5 (3 months after surgery)	Visit 6 (1 year after surgery)	Visit 7 (3 years after surgery)
Signed informed consent	X						
Inclusion/exclusion criteria	X						
Demographic data	X						
Medical insurance type	X						
Delayed visit and admission	X						
Previous history of diseases	X						
Previous history of drug	X						
Risk factors	X						
Disease attack and admission *	X						
Type of hernia (indirect hernia, direct hernia)	X						
Vital sign†	X						
Laboratory examination ‡	X	X					
Imaging examination §	X						
Electrocardiography	X						
Treatment regimen ¶		X					
VAS score **						X	X
SF-36 score			X	X	X	X	X
Medical cost		X	X	X	X	X	X
Concomitant treatment	X	X					

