### Study completion/termination

#### Study completion

When the last visit of the last participant is completed, the research centre will inform the sponsor, and study completion will be designated. The sponsor will inform all research centres of the time of study completion. Further research after this time must be approved by the sponsor and can then be performed without protocol supplements.

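### The stated recruitment and data-collection dates cannot both hold with a primary outcome assessed 1 and 2 years after surgery

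*Protocol article*

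**What the plan says.** All references are to the protocol article.

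- **Dates.** The Abstract (Methods and analysis) states "Actual study start date is 6 February 2017" and "Estimated study completion date is June 2020". The Ethical approval section states "We began recruitment in February 2017 and expect to have completed recruitment by December 2019 and completed data collection by June 2020".
- **Primary outcome.** Under Primary outcome measure, "the incidence of chronic pain at 1 and 2 years after surgery will be evaluated".
- **Visits.** The Follow-up section lists "Visit 7 (2 years after surgery via telephone follow-up)VAS pain score". After surgery the VAS is scheduled only at Visits 6 (1 year) and 7, both there and in Table 3.
- **Table 3.** The column for the last visit reads "Visit 7 (3 years after surgery", whereas the Abstract, Study design, Follow-up and both outcome sections put the last assessment at 2 years.
- **End of study.** Under Study completion, completion is designated "When the last visit of the last participant is completed".

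**The concern.** The interval from the end of recruitment (December 2019) to the end of data collection (June 2020) is about six months. The primary outcome needs one and two years. Patients recruited late therefore cannot reach the visits at which it is measured before the stated close. Because no VAS is scheduled between surgery and 1 year, a patient who reaches neither Visit 6 nor Visit 7 has no scheduled score from which the primary outcome could be determined.

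If the dates were applied as written, the primary outcome would be missing by calendar for a sizeable share of randomised patients. That would cut the power on which the sample size rests and weaken the intention-to-treat comparison promised under Statistical analysis.

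**Working it through.** **1. The plan's own sample size.** Inputs from the Sample size section: p1 = 0.10, p2 = 0.034, α = 0.05 (taken as two-sided), power 90%. With p̄ = 0.067, the pooled-variance formula per arm is

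n = [1.960·√(2p̄(1−p̄)) + 1.282·√(p1(1−p1) + p2(1−p2))]² / (p1−p2)²

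= [1.960 × 0.3536 + 1.282 × 0.3505]² / 0.066² ≈ 299.5, so 300 per arm and 600 in total. This matches the stated 600, so the same method is used for power below. The stated 720 is 600 × 1.2. After 20% loss, 720 × 0.8 = 576 remain, with power 88.8%. The fair baseline is therefore about 89%.

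**2. The last patient.** Surgery in December 2019 puts the 1-year visit in December 2020 and the 2-year visit in December 2021, which is 6 and 18 months after June 2020. For everyone to reach 2 years by June 2020, recruitment would have to end by about June 2018. For 1 year, it would have to end by about June 2019.

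**3. Share reaching each visit.** Assumptions: recruitment from 6 February 2017 to 31 December 2019 (1058 days), close on 30 June 2020, surgery at recruitment, uniform accrual.

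- 2 years: recruited by 30 June 2018, 509/1058 = 48.1%, so 51.9% miss it.
- 1 year: recruited by 30 June 2019, 874/1058 = 82.6%, so 17.4% miss it.

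Varying the unstated days within the stated months moves these to 50%–56% and 15%–21%.

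**4. Other accrual patterns.** The documents give none. With t the elapsed fraction of the window (0.481 and 0.826), the share recruited is t² if accrual rises linearly from zero and 1−(1−t)² if it falls linearly to zero.

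**5. Power at 10% versus 3.4%.** With n per arm,

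power = Φ{[(p1−p2)√n − 1.960√(2p̄(1−p̄))] / √(p1(1−p1) + p2(1−p2))}

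| Accrual | Visit | Cannot reach it | Can reach it, of 720 | Power, no other loss | After 20% loss | Power |
|---|---|---|---|---|---|---|
| Falling | 2 years | 27% | 526 | 86% | 421 | 77% |
| Uniform | 2 years | 52% | 346 | 69% | 277 | 59% |
| Rising | 2 years | 77% | 167 | 40% | 133 | 33% |
| Falling | 1 year | 3% | 698 | 94% | 559 | 88% |
| Uniform | 1 year | 17% | 595 | 90% | 476 | 82% |
| Rising | 1 year | 32% | 491 | 84% | 393 | 75% |

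At 2 years, power is below 90% in every row, even with no other loss. At 1 year the result depends on the accrual pattern and on the planned loss.

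**The case against.** The strongest reply is that the dates are forecasts, worded as estimates and expectations, whereas the rule under Study completion ties the end to the last participant's last visit. Nothing in the article orders a data cut or administrative censoring in June 2020. If the completion rule governs, follow-up simply continues and no outcome is lost. Equally, December 2019 appears once and June 2020 twice. If the recruitment end date is the slip, recruitment ending in about June 2018 would give everyone a 2-year visit. This stands: the documents do not settle which date is wrong, and the loss arises only if both are enforced.

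The article also partly contemplates shorter follow-up. The section on completion and withdrawal counts at least one year of data as a complete case, and the section on AE reporting lets the research period end between one and two years after surgery. This softens the 2-year gap. It does not cover patients operated on after June 2019, and it does not alter the 2-year time point of the primary outcome.

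Three stronger readings are tempting, and the documents do not support them:

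- A reader might infer that half the patients will lack a 2-year outcome and a sixth a 1-year outcome. Those shares need uniform accrual and both dates enforced, and the article states neither condition.
- A reader might infer that the planned power is out of reach at both time points because of the calendar. At 1 year under uniform accrual, power is about 90% with no other loss. Part of the gap to 90% after loss comes from inflating 600 to 720, which leaves 576.
- A reader might take Table 3 to mean a planned 3-year visit and a still larger gap. Every other mention says 2 years, so it reads as a slip to be reconciled.

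**Conclusion.** The inconsistency is certain and needs no assumption: recruitment to December 2019, a close in June 2020, 1- and 2-year primary assessments, and completion at the last participant's last visit cannot all be true. It is an internal contradiction, and nothing shows that truncated follow-up was chosen.

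The size is conditional on enforcing both dates and on the accrual pattern. With the planned loss, the drop from the 89% baseline is about 30 percentage points at 2 years and about 7 at 1 year under uniform accrual. At the favourable end of the range (falling accrual) it is about 12 points at 2 years and about 1 at 1 year. The 2-year shortfall is therefore the robust finding. It should be corrected because it concerns whether the primary outcome can be observed at all in late recruits.

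**What to change.** Make the dates consistent in the Abstract and in the Ethical approval section, in one of two ways, according to which date the sponsor intends:

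- restate the end of data collection and study completion as the last patient's 2-year visit, which is December 2021 if recruitment ends in December 2019; or
- if June 2020 is the intended close, correct the end of recruitment to about June 2018.

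In either case, state that the final 2-year analysis is not run until all patients have reached that visit. Reconcile the Visit 7 column of Table 3 with the 2-year visit given elsewhere.

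Moving the close delays the final report by up to 18 months. It adds no patients and no visits, because the 2-year telephone follow-up is already promised to every patient. Ending recruitment earlier keeps the close date but requires the 720 patients to be recruited in a window about 18 months shorter.
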